## Results

### Analysis plan-primary aim: academic achievement

Changes (year 3 minus baseline) in academic achievement (WIAT-III comprehensive score) will be compared between students attending A + PAAC intervention and control schools using a modified two-sample *t*-test adjusted for the intra-class correlation (ICC) [41] with a type I error rate of 5%. Similar analysis will be completed for WIAT-III sub-scales and for each of the secondary endpoints (Kansas State Assessment, cognitive function, BMI, cardiovascular fitness, attention-to-task, daily physical activity). This longitudinal study will provide multiple assessments over time; therefore linear mixed models will be used to assess differences in between A + PAAC and control in the primary and secondary endpoints. A compound symmetric correlation structure for estimating the intraclass correlation coefficient (ICC) within a school is assumed.

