## Methods

### Study design and setting

Seventeen elementary schools in northeast Kansas were stratified by school district and cluster randomized to receive A + PAAC (N = 9) or serve as non-intervention controls (N = 8). Schools will be monetarily compensated for participation; 50% following randomization and 50% at study completion. All classroom teachers in A + PAAC schools were trained to deliver two 10-minute physically active academic lessons 5 days/week over the 3-year intervention. Teachers in control schools were asked continue to use traditional classroom instruction and students in both intervention and control schools will continue with their typical PE schedule (2–30 minute classes/week). A random sample of 2^nd^ and 3^rd^ grade students in each school was selected from those who provided parental consent/child assent (stratified by grade and gender) to complete outcome assessments including academic achievement, cognitive function, cardiovascular fitness, daily physical activity, and BMI at baseline (Fall 2011) and at the end of the spring semester for the next 3 years (2012–2014). Only students in 2^nd^ and 3^rd^ grade at baseline were assessed, as they will remain in elementary school for the duration of the 3-year intervention. School and student recruitment school randomization, teacher training, and baseline testing for A + PAAC have been completed. This study was approved by the Human Subjects Committee at the University of Kansas (HSCL #13460).

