### Recruitment

The parents of students in grades 2 and 3 in both the A + PAAC and control schools received a brief flyer describing the study, including exclusion criteria and assessment procedures. Parents of students interested in participation returned a portion of the flyer providing their contact information to the school. The parents were then invited to attend an informal meeting at the school with both study staff and classroom teachers where the study was described. Descriptive characteristics of both the intervention and control schools are presented in Table 1.

**Table 1 T1:** Descriptive characteristics of schools participating in the study

	**Intervention**	**Control**
Total School Enrollment	369.7 ± 96.6	385 ± 121.9
Total 2^nd^ and 3^rd^ Grade Enrollment (N = 1902)	978	924
2^nd^ and 3^rd^ Grade Class Size	22.5 ± 5.3	20.4 ± 2.6
Urban/Rural Schools (n/n)	6/3	6/2
Minority (%)	23.8	30.2
Free/reduced lunches (%)	35.3	42.5

Values are N’s or mean ± standard deviation.

Students with physical or intellectual disabilities or learning disorders will receive A + PAAC or control as a function of attending a participating school; however, some students were ineligible to complete outcome assessments due to their disability (i.e. blind, severe intellectual disability, etc.). Baseline participant characteristics by intervention group are presented in Table 2.

**Table 2 T2:** A + PAAC: participant baseline characteristics

	**Intervention** **(n = 370)**	**Control** **(n = 317)**
Age (years)	7.6 ± 0.6	7.6 ± 0.6
Height (cm)	129.6 ± 6.5	129.6 ± 6.9
Weight (kg)	29.6 ± 7.2	29.6 ± 7.7
Waist (cm)	57.6 ± 7.5	57.1 ± 7.7
BMI Percentile	61.1 ± 29.3	61.1 ± 30.0
Female (%)	47.9	53.1
Minority (%)	16.3	23.2
Free/reduced lunches (%)	26.5	36.7

Values are mean ± standard deviation unless otherwise indicated.

*Note*. 698 students were randomized. 687 performed anthropometric testing.

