### Sample size/power

The primary aim of this study is to compare change in academic achievement (comprehensive score) between the two treatments (A + PAAC vs. control). Power calculations were based on results from a secondary analysis of change in academic achievement from the completed PAAC study [10,11]. Since this is a cluster randomized design or an inherent ICC within the schools was assumed. The primary analysis will be conducted using a modified two-sample *t*-test [41] using a type I error rate of 5%. Table 3 describes the power for a range of ICCs, number of schools per treatment, and sample sizes within each school assuming an expected improvement in academic achievement of 5 points in the A + PAAC group, no change in the control group with a common standard deviation of 9 points, similar to results from the PAAC study [10].

**Table 3 T3:** Statistical power

**Schools per treatment**	**Students per school**	**Intra-Class correlation**					
		**0**	**0.01**	**0.03**	**0.05**	**0.07**	**0.1**
6	20	0.99	0.98	0.93	0.87	0.8	0.71
6	30	0.99	0.99	0.97	0.92	0.86	0.76
7	20	0.99	0.99	0.96	0.91	0.86	0.78
7	30	0.99	0.99	0.99	0.95	0.9	0.82

An ICC in the range of 0.03 to 0.07 is anticipated for academic achievement, thus to ensure at least 85% power for this confirmatory study, 17 schools were randomized between the two treatment groups with 40 students being recruited per school. Based on the power analysis above, power will be sufficient with as few as 20 students per school and ICCs as high as 0.10. Given the limited preliminary data, exact power calculations are not possible for the secondary endpoints. However, assuming a type I error rate of 5%, secondary endpoints have the following power: 0.99, 0.99, 0.96, 0.91, 0.84 and 0.74, to detect an effect size of 0.5 standard deviations for ICCs equal to 0, 0.01, 0.03, 0.05, 0.07 and 0.10, respectively. Thus, the study will have sufficient power to detect any clinically meaningful difference on the secondary endpoints.

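### The named primary test, an ICC-adjusted t-test on change scores, has no term for the district strata and no regression adjustment for baseline WIAT-III, so it is valid but less precise than it could be

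*Protocol article*

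**What the plan says.** All references are to the protocol article.

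- **Analysis plan, primary aim.** "Changes (year 3 minus baseline) in academic achievement (WIAT-III comprehensive score) will be compared between students attending A + PAAC intervention and control schools", with a two-sample t-test "adjusted for the intra-class correlation (ICC) [41] with a type I error rate of 5" per cent. No covariate or stratum is named.
- **Sample size/power.** This section confirms which analysis is primary: "The primary analysis will be conducted using a modified two-sample" t-test.
- **Analysis plan, primary aim, later sentence.** Because there are repeated assessments, "therefore linear mixed models will be used to assess differences in between A + PAAC and control in the primary and secondary endpoints". Correlation within school is taken to be compound symmetric. Fixed effects other than the group comparison are not listed.
- **Study design and setting.** The 17 schools "were stratified by school district and cluster randomized to receive A + PAAC" (9 schools) or control (8 schools).
- **Exploratory analysis.** Baseline characteristics appear only here, as candidate predictors of change in a stepwise model. Neither district nor free/reduced-lunch status is on that list.
- **Table 2.** Free/reduced lunch is 26.5% in the intervention arm and 36.7% in the control arm; minority share is 16.3% and 23.2%. Baseline WIAT-III by arm is not reported.

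**The concern.** Two features of the design are not carried into the test that the article calls primary.

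First, randomisation was restricted within districts. An analysis without a district term leaves between-district variation in the error, although stratification has removed much of it from the difference between arms. The standard error is then too large, and with only 17 randomised units that can matter.

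Second, a change score fixes the coefficient of baseline at 1. Regression on baseline estimates that coefficient and, with equal variances at the two times, never has a larger residual variance.

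What is at stake is precision and an actual type I error below the nominal 5%. Type I error is not inflated.

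**Working it through.** **Inputs from the article (Sample size/power):** difference 5 points, SD of change 9, ICC anticipated at 0.03 to 0.07 and tabulated up to 0.10, 40 students per school, target power at least 85%. Schools: 9 v 8. **Not given:** the baseline-to-year-3 correlation r, the number of districts, and the share of between-school variance that district explains. These are assumed below and shown as ranges.

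**Step 1. Reproduce Table 3.** With k schools per arm and m students per school, the design effect is 1 + (m − 1) × ICC, the effective n per arm is km divided by the design effect, and power = Φ(5 / [9 × √(2/n)] − 1.96).

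Example, 6 schools × 20 students at ICC 0.10: design effect 1 + 19 × 0.10 = 2.9; n = 120/2.9 = 41.4; SE = 9 × √(2/41.4) = 1.98; 5/1.98 = 2.53; power = Φ(0.57) = 0.715. The table has 0.71. All 24 cells reproduce within 0.02. The sample size therefore rests on the same comparison, without strata or covariates. The steps below use school-level degrees of freedom (17 − 2 = 15 without district terms).

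**Step 2. Baseline as covariate.** With common score variance s², the change-score variance is 2s²(1 − r) and the variance after regression on baseline is s²(1 − r²). The ratio is (1 + r)/2. Power for 9 v 8 schools and 40 students per school, with the ratio applied to the whole variance:

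| Analysis | Variance ratio | Power, ICC 0.07 | Power, ICC 0.10 |
|---|---|---|---|
| Change score | 1 | 0.938 | 0.863 |
| Baseline-adjusted, r = 0.9 | 0.95 | 0.948 | 0.879 |
| Baseline-adjusted, r = 0.7 | 0.85 | 0.966 | 0.911 |
| Baseline-adjusted, r = 0.5 | 0.75 | 0.981 | 0.941 |

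The SD of 9 narrows r only if a score SD is assumed, because r = 1 − 81/(2s²). For s = 12, r = 0.72; for s = 15, r = 0.82. The ratio is then 0.86 to 0.91, a variance 9% to 14% lower.

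**Step 3. District terms.** Simulation with four assumed districts of 5, 4, 4 and 4 schools, 40 students per school, ICC 0.10 and 8,000 trials per cell. The t-test on school means has 15 degrees of freedom; the analysis with district terms has 12.

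| Share of between-school variance due to district | Type I error, no district term | Type I error, district terms | Power, no district term | Power, district terms |
|---|---|---|---|---|
| 0% | 0.049 | 0.050 | 0.87 | 0.86 |
| 30% | 0.031 | 0.049 | 0.90 | 0.93 |
| 50% | 0.022 | 0.050 | 0.91 | 0.97 |
| 80% | 0.010 | 0.053 | 0.94 | 0.999 |

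**Step 4. The Table 2 differences.** Lunch status: 36.7 − 26.5 = 10.2 points, standardised difference 0.22. Minority share: 23.2 − 16.3 = 6.9 points, standardised difference 0.17. Ignoring clustering, z is −2.88 and −2.28. With an assumed ICC of 0.05 to 0.20 for these traits, z is −1.67 to −0.97 for lunch status and −1.32 to −0.76 for minority share. Both gaps are compatible with chance among 17 clusters.

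**The case against.** The strongest reply is that nothing here is broken. Change-score and baseline-adjusted analyses are both valid under randomisation. The test already uses the baseline score, by subtraction, and already allows for clustering. Leaving out the strata makes it conservative. Power at the anticipated ICCs exceeds 85% as planned (0.938 at ICC 0.07 with 40 students per school). If district explains nothing, district terms cost about 0.01 in power. A mixed model is also planned for the primary endpoint, and a condensed article may leave its covariates to the full plan. All of this stands, and it limits the size of the point. It does not remove it, because the article itself designates the t-test as primary, and that test omits the randomisation stratum.

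A reader might infer two stronger things.

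- *That the imbalance biases the result in favour of the intervention.* The documents do not support this. Baseline WIAT-III by arm is not reported, a stable difference in level cancels in a change score, and any bias figure needs an assumed difference in three-year change between lunch groups. If control children had started lower by chance, regression to the mean would work against the intervention.
- *That the imbalance arose from recruitment after allocation.* The Recruitment section says "The parents of students in grades 2 and 3 in both the A + PAAC and control schools received a brief flyer", but it does not say that flyers followed allocation, and Study design and setting lists recruitment ahead of randomisation. The lunch gap is 7.2 points in the schools (Table 1: 35.3% v 42.5%) and 10.2 in participants. That is 3.0 points wider, against a sampling SE of about 3.5 points for the participant gap even before clustering: √(0.265 × 0.735/370 + 0.367 × 0.633/317). The minority gap barely moves, from 6.4 (23.8% v 30.2%) to 6.9 points.

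**Conclusion.** The point holds as a matter of efficiency and of matching the analysis to the randomisation. The primary t-test is valid, but it is less precise than a baseline-adjusted analysis. It is also conservative to the extent that district explains between-school variation in change.

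The gain from baseline adjustment is a variance 5% to 25% lower for r from 0.9 to 0.5, assuming equal variances at the two times. The effect of district could be anywhere from a loss of about 0.01 in power to a clear gain, depending on the number and effect of districts, which the article does not give; the simulated figures hold for four districts only. The type I errors near 0.05 or below assume school-level degrees of freedom. The Table 2 differences justify a sensitivity analysis. They do not show bias or selective recruitment.

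**What to change.** Before year-3 data are analysed, make the primary analysis a linear mixed model for year-3 WIAT-III with arm, baseline WIAT-III and district as fixed effects and school as a random effect, using school-level degrees of freedom for the arm comparison. Grade and gender, the sampling strata, may be added. State that this is the mixed model already mentioned for the primary endpoint, so that one analysis is designated primary.

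Keep the change-score t-test as a sensitivity analysis. Add a second one that also adjusts for free/reduced-lunch status. It belongs there because it is prompted by a difference already seen in Table 2.

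The cost is wording: baseline WIAT-III, district, grade, gender and lunch status are already recorded. The statistical price is one school-level degree of freedom for each district beyond the first (15 becomes 12 with four districts). If some districts contain a single school, say in advance how they are pooled, because they carry no within-district comparison of arms.

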### Academic achievement

Academic achievement was assessed using the Weschsler Individual Achievement Test-Third Edition (WIAT-III) [23] and the Kansas Assessment, a standardized academic achievement test administered to 3^rd^ through 12^th^ grade students annually by the state of Kansas. The WIAT-III was individually administered by research staff trained and supervised by a qualified co-investigator. Five WIAT-III subtests (reading comprehension and oral reading fluency, spelling, and mathematics problem solving and numerical operations) were selected and take approximately 40–50 minutes to complete. The WIAT-III has excellent inter-scorer reliability (i.e., 0.92 to 0.99), internal consistency, split-half method (e.g., by age-range from 0.83 to 0.98), and test-retest stability (e.g., for children 6 to 12 years of age, 0.87 to 0.96 over 2 to 32 days). Validity is supported via item reviews of curriculum experts and by correlations with other tests, including the WIAT-II (e.g., .62 to .86), and measures of academic achievement (e.g., 0.60 to 0.82) [23]. The WIAT-III was scored by the research staff and all tests were checked for accuracy by a trained investigator. Any discrepancy in scores between examiner and the research team member was resolved by a co-investigator. All scores were entered into the WIAT-III computerized scoring assistant, which automatically disallows out-of-range values and computes subtest and composite scores. In addition to WIAT-III, the individual results of the Kansas State Assessment (KSA) standardized achievement tests will be obtained. These tests evaluate performance on the Kansas State standards, which define what students should be learning each year and are administered annually to children in grades 3 and higher. Two years of results for children initially in 2^nd^ grade and 3 years of results for children initially in 3^rd^ grade will be obtained.

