### Attention-to-task

Attention-to-task will be assessed by trained research staff on the same random schedule for recording classroom physical activity, described in the process evaluation section below, using a modification of the procedures from Mahar et al [33]. During each assessment, approximately 5 students will be observed for 5 minute, 20 minutes before and 20 minutes after an A + PAAC activity or non-active lesson in control schools. Each child will be observed for 10 seconds, after which the appropriate behavior code will be circled. This procedure will be repeated over the 5 minute interval to result in a total of ~ 20 observations per child. Coding includes on-task, motor off-task, noise off-task, or passive/other off-task [34,35].

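### The change-from-baseline t-test is extended to the Kansas State Assessment, which by the article's own account has no baseline for initial 2nd graders and, unless given in early fall, none for initial 3rd graders

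*Protocol article*

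**What the plan says.** Under *Analysis plan-primary aim: academic achievement*, the protocol article sets the main comparison: "Changes (year 3 minus baseline) in academic achievement (WIAT-III comprehensive score) will be compared" between arms by a modified two-sample t-test "adjusted for the intra-class correlation (ICC) [41] with a type I error rate of 5" per cent. The next sentence extends it: "Similar analysis will be completed for WIAT-III sub-scales and for each of the secondary endpoints (Kansas State Assessment", followed by the remaining secondary endpoints. No exception is made for the Kansas State Assessment (KSA). The paragraph then adds that "linear mixed models will be used to assess differences in between A + PAAC and control in the primary and secondary endpoints".

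Under *Academic achievement*, the Kansas tests "are administered annually to children in grades 3 and higher". The expected yield is also given: "Two years of results for children initially in 2^nd^ grade and 3 years of results for children initially in 3^rd^ grade will be obtained".

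Under *Research staff training and blinding*, the article states without exception that every outcome was measured in Fall 2011 and will be measured again each spring for three years.

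**The concern.** A year-3-minus-baseline change needs two values per child, and the KSA's schedule does not supply the first. The analysis section and the blanket baseline statement both treat the KSA like the other outcomes; the section describing the test shows that it is not.

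The KSA is the only achievement measure besides the WIAT-III. An analyst who follows the change rule for it will have to improvise: drop children without a baseline, let the first available score stand in, impute a baseline, or abandon the change score. These choices answer different questions. Making the choice after scores are seen leaves room for selection.

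**Working it through.** **Inputs from the article**
- Grades at entry: 2 and 3 (*Study design and setting*).
- Schedule: baseline in Fall 2011, then spring 2012, 2013 and 2014 (same section).
- KSA: once a year, from grade 3 (*Academic achievement*).
- Stated yield: 2 results (initial 2nd graders), 3 results (initial 3rd graders) (same section).

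**Step 1: reproduce the stated yield.** A child entering in grade g is in grade g + j − 1 in study year j (j = 1, 2, 3). A result exists when g + j − 1 ≥ 3.

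| Entry grade | Grade before entry | Year 1 (2011–12) | Year 2 (2012–13) | Year 3 (2013–14) | Results |
|---|---|---|---|---|---|
| 2 | 1: no test | grade 2: no test | grade 3: KSA | grade 4: KSA | 2 |
| 3 | 2: no test | grade 3: KSA | grade 4: KSA | grade 5: KSA | 3 |

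The counts of 2 and 3 match the article exactly.

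**Step 2: compare with what the change rule needs.** Baseline plus three springs is 1 + 3 = 4 occasions. The KSA supplies 2 or 3.
- Initial 2nd graders: first score in study year 2. There is no baseline under any reading, so year 3 minus baseline is undefined for all of them.
- Initial 3rd graders: no test in the grade before entry, so the first of the three scores falls in study year 1. It precedes the lessons only if the test is given in early fall. The article does not state the time of year. If it is given in early fall each year, the third score comes early in study year 3, after about two years of lessons rather than three.

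**Step 3: what happens if the first available score stands in as baseline.** The article does not propose this; it is a likely workaround. Let δ(t) be the difference between arms after t years. A change from a first score at time t0 estimates δ(3) − δ(t0), so the share of the year-3 effect retained is 1 − δ(t0)/δ(3). If testing falls late in the school year (assumption), t0 = 1 for initial 3rd graders and t0 = 2 for initial 2nd graders.

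| Assumed build-up of effect | Initial 3rd graders | Initial 2nd graders |
|---|---|---|
| Linear over 3 years | 1 − 1/3 = 2/3 | 1 − 2/3 = 1/3 |
| Complete by the first score | 0 | 0 |
| None until after the first score | 1 | 1 |

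As long as the effect at the first score has the same sign as at year 3 and is no larger, the bias is toward zero. Its size depends wholly on the assumed build-up and on the mix of grades; the article gives neither.

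**The case against.** **The mixed model.** The same section says mixed models will be used for the secondary endpoints. Such a model can compare arms on the two or three available scores without a baseline. This stands. A reader might infer that the KSA cannot be analysed at all, but the article does not support that; only the change-score t-test fails. The article does not say, however, which of the two analyses governs or how the unequal score histories are handled.

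**Similar is not identical, and an article condenses.** The year-3-minus-baseline definition is attached by name only to the WIAT-III, and endpoint-specific detail may sit in a fuller document. This softens the point but does not remove it. The KSA is named first among the endpoints to which the analysis is carried over, and the statement that all outcomes had a baseline is unqualified. These are statements at odds with each other, not omissions.

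**Multiple imputation.** The *Missing data* section plans model-based imputation. It cannot credibly create a baseline on a test that was not given in grade 2. Unless testing is in early fall, no child has an observed baseline from which to build the model.

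**Attention-to-task.** A reader might infer the same defect there, because the list in *Study design and setting* omits it and its own section uses the future tense: "Attention-to-task will be assessed by trained research staff on the same random schedule for recording classroom physical activity". The documents do not support that reading. The abstract puts this mediator on the WIAT-III schedule, the staff-training section covers all outcomes, and the exploratory analysis relies on baseline levels of the mediators. In control schools the observation is made around an ordinary lesson, so it could be made in either arm before the intervention.

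**A fixed size of bias, or a fixed loss of sample.** A reader might take the fractions above as the trial's expected bias, or assume that half the children lack a baseline. Neither is supported. The substitution is hypothetical, and the article gives no count of students by grade.

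**Conclusion.** The change-score rule cannot be carried out for the KSA as written. For initial 2nd graders this is certain. For initial 3rd graders it holds unless the test is given in early fall before lessons start, which the article neither states nor excludes. If the first score is used as a substitute baseline, the estimate is biased toward zero under the sign condition above. Anything from none to all of the year-3 effect could be lost, and one third to two thirds of it under linear build-up with late-year testing.

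Severity is moderate. The KSA is a secondary endpoint and is not among the mediators. The primary WIAT-III comparison and its sample size do not depend on it, and a workable method is already named in the same paragraph.

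**What to change.** 1. In the primary-aim analysis section, exempt the KSA from the change-from-baseline rule. In the staff-training section, exempt it from the statement that all outcomes were assessed at baseline.
2. State a KSA-specific analysis: compare post-randomisation scores between arms, with year 3 as the main time point, in a mixed model with a school random effect, adjusted for grade, district (the randomisation stratum) and baseline WIAT-III. The grade term is needed because at year 3 the two cohorts sit the grade 4 and grade 5 tests. Baseline WIAT-III does the job that the missing KSA baseline cannot, without subtracting a score already exposed to the intervention.
3. State when in the school year the KSA is given.

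The cost is wording, best settled before KSA outcomes are seen by arm. No measurement beyond those planned is needed: the baseline WIAT-III has been taken, and the article already plans to obtain the KSA results.

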### Missing data

Predictive model-based multiple imputation will be used to impute missing data. Since the primary longitudinal models are a mixed linear regression, using a predictive model-based approach will allow for the use of more actual data to impute the missing data. The rate of missing data over time will be examined to determine if treatment, baseline weight, gender, age, and/or school are related to the missing data. If none of these factors is related to the missing data, it might be safe to assume data are missing completely at random.

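### The only correlation structure stated for the longitudinal mixed models, compound symmetry within school, suits one change score per child but not repeated scores

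*Protocol article*

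**What the plan says.** The section on the primary-aim analysis describes two analyses of the same endpoint.

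- **Change-score test.** "Changes (year 3 minus baseline) in academic achievement (WIAT-III comprehensive score) will be compared between students" by a two-sample t-test adjusted for the ICC. The Sample size/power section calls this test the primary analysis and builds Table 3 on it.
- **Mixed models.** "This longitudinal study will provide multiple assessments over time; therefore linear mixed models will be used to assess differences" between arms in the primary and secondary endpoints. The next sentence gives the structure: "A compound symmetric correlation structure for estimating the intraclass correlation coefficient (ICC) within a school is assumed". The section names neither a child-level term nor a school-by-time term, and it excludes neither.

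Under Study design and setting, children are assessed "at baseline (Fall 2011) and at the end of the spring semester for the next 3 years (2012–2014"), which makes four occasions. The Missing data section gives the mixed models a prominent place: "Since the primary longitudinal models are a mixed linear regression". The Exploratory analysis section assumes the same within-school compound symmetry for models that predict change in achievement.

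**The concern.** The mixed models are justified by repeated assessments, but the structure named for them describes only how children in one school resemble each other. Two things matter for an arm-by-time contrast, and neither is in that structure.

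1. **Scores of the same child.** Under school-only compound symmetry, a child's baseline and year 3 scores are correlated no more than the scores of two classmates. The Academic achievement section reports "test-retest stability (e.g., for children 6 to 12 years of age, 0.87 to 0.96 over 2 to 32 days") for the WIAT-III. That is a short interval, but it suggests that the within-child correlation is well above the anticipated ICC of 0.03 to 0.07. Leaving it out makes the standard error of change too large.
2. **Schools that change by different amounts.** A constant school effect drops out of year 3 minus baseline. The clustering of change, which is what the power calculation allows for, is then missing from the contrast. Leaving it out makes the standard error too small.

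The two errors pull in opposite directions. Their net effect depends on the within-child correlation of each outcome, so a reader of the results could not correct for it.

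**Working it through.** **Inputs from the article.** 9 and 8 schools; 40 students per school (m); anticipated ICC 0.03 to 0.07; effect 5 points; SD 9 points, read here as the SD of change; type I error 5%, taken as two-sided.

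**Assumed.** The within-child correlation over three years, ρ, is not given. I use 0.5 to 0.87, the upper end being the lowest short-term retest figure. I also assume balanced data, time as a category, and an ICC of change that arises from school-by-time variance.

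**Step 1: the plan's own figure.** Table 3, 6 schools per arm, 20 students, ICC 0.05. The design effect is 1 + 19 × 0.05 = 1.95, so the effective n per arm is 120/1.95 = 61.5. The SE is 9 × √(2/61.5) = 1.62 and 5/1.62 = 3.08. Power is Φ(3.08 − 1.96) = 0.87, as printed. All 24 cells reproduce within 0.02. Table 3 therefore describes a comparison of change scores with an ICC of change.

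**Step 2: true SE of the arm difference in change.** Let DE = 1 + 39 × ICC, which is 2.17, 2.95 and 3.73 at ICC 0.03, 0.05 and 0.07.

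True SE² = 81 × DE/40 × (1/9 + 1/8), so the SE is 1.02, 1.19 and 1.34.

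**Step 3: SE from school-only compound symmetry.** Let s be the score SD. The model treats a child's two scores as independent given school:

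Model SE² = 2s²/40 × (1/9 + 1/8), where 2s²(1 − ρ) = 81.

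Hence model SE / true SE = 1/√[(1 − ρ) × DE]. The type I error is 2Φ(−1.96 × ratio).

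Each cell gives the SE ratio, then the type I error by formula / in 1,000 simulated trials with 9 and 8 schools, 40 students and 4 waves.

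| ρ | Implied score SD | ICC 0.03 | ICC 0.05 | ICC 0.07 |
|---|---|---|---|---|
| 0.5 | 9.0 | 0.96; 0.060 / 0.071 | 0.82; 0.107 / 0.119 | 0.73; 0.151 / 0.155 |
| 0.7 | 11.6 | 1.24; 0.015 / 0.025 | 1.06; 0.037 / 0.046 | 0.95; 0.064 / 0.055 |
| 0.8 | 14.2 | 1.52; 0.003 / 0.006 | 1.30; 0.011 / 0.015 | 1.16; 0.023 / 0.024 |
| 0.87 | 17.7 | 1.88; <0.001 / 0.000 | 1.61; 0.002 / 0.002 | 1.44; 0.005 / 0.008 |

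The formula ignores the stable between-school share of the score variance, which lowers the model SE slightly. With a share of 0.10 the factor is √0.9 = 0.95.

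**Step 4: cost in power when the test is conservative.** Take score SD 17.5, stable school share 0.10 and ICC of change 0.05. The model SE is √(2 × 306.25 × 0.9/40 × 0.2361) = 1.80, so the test rejects beyond 1.96 × 1.80 = 3.54. Power for 5 points is Φ((5 − 3.54)/1.19) = 0.89. A correctly specified contrast has about 0.98.

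**Step 5: child effect present, school-by-time still absent.** The model SE then uses the right change variance but omits DE, so the ratio is 1/√DE = 0.68, 0.58 and 0.52. The type I error is 0.18, 0.25 and 0.31. Simulation gave 0.18 to 0.33 over the same ICCs.

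**Step 6: an analysis that respects both features.** A t-test on the school means of change, with 15 degrees of freedom, had a type I error of 0.038 to 0.065 in every setting simulated.

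**The case against.** Four objections deserve weight.

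- **The sentence does not say it is the whole model.** It explains how the school ICC is handled, and a condensed article may leave the remaining random effects to a fuller plan. This stands: that the plan ignores within-child correlation is an inference. It does not remove the point, because supplying the child effect alone leads to Step 5, where the constant school effect still cancels.
- **The sentence may refer to a model of change with one record per child.** Compound symmetry within school would then be right, as it is in the Exploratory analysis section if change is the outcome. But the sentence directly follows the one that justifies mixed models by multiple assessments, so this is not its natural reading.
- **The trial is powered on the t-test.** This stands. A reader might infer that the primary comparison or Table 3 is invalid. Neither is: both use one change per child and an ICC of change that absorbs school drift. The mixed models still cover the primary endpoint and are called primary under Missing data.
- **The size is undetermined.** This stands too. If ρ is near the retest figures, the literal model is conservative. At ρ 0.7 and ICC 0.05 the two errors nearly cancel (ratio 1.06). Type I errors above 10% need ρ near 0.5 together with an ICC of 0.05 or more.

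**Conclusion.** The point holds for the longitudinal mixed models and only for them. The one structure the article states does not fit repeated scores, whether it is read literally or with a child effect supplied.

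- **Literal reading:** the SE is 0.73 to 1.88 times the true value at 40 per school, ICC of change 0.03 to 0.07 and ρ 0.5 to 0.87. The type I error ranges from under 1% to about 15%.
- **Child effect implied, no school-by-time effect:** type I error of about 18% to 31%.

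A reader might infer that the mixed-model standard errors will be wrong in a known direction. The article does not support that, because it gives neither the three-year within-child correlation nor the score SD. These figures also rest on reading 9 points as the SD of change.

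Four occasions applies to the WIAT-III. The Kansas assessment gives two or three results per child; the same reasoning applies wherever its models use repeated scores, but the figures above were not computed for it.

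**What to change.** In the primary-aim analysis section, replace the sentence on correlation structure with one that separates the two kinds of model:

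- **Models of repeated scores:** a random school effect, a school-by-time effect (or school-specific change), and a within-child correlation over waves (child random intercept or unstructured), all three together. Test the arm-by-time contrast with small-sample degrees of freedom based on the 17 schools.
- **Models with one change value per child:** keep the single within-school compound symmetry.

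The child effect should not be added alone, since Step 5 shows that this makes the test clearly anti-conservative. It would also help to say whether the t-test or the mixed model is primary, because the Sample size/power and Missing data sections use that word for different analyses.

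The cost is a sentence or two of text and slightly more model code. Intervals may be wider than under the stated structure where schools change by different amounts. Data collection, sample size and Table 3 do not change.
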